### Outcome measures

The primary endpoint is overall survival, which will be followed up until 60 months after discharge of surgery. The key secondary endpoints are complete resection (R0), post-operative complications according to the Esophageal Complications Consensus Group (ECCG) definitions [18] and scored on severity by the the Clavien-Dindo classification [19], number and localization of tumor infiltrated lymph nodes at dissection, disease-free survival, quality of life (EORTC QLQ-C30, QLQ-STO22, and QLQ-OG25 after 3, 6, 9, 12, 18, 24 months) and cost-effectiveness.

After consolidation of the EORTC questionnaires data during the course of the trail, a cost effectiveness analysis of both procedures based on direct costs and resulting QALYs will be performed and the incremental cost-effectiveness ratio will be calculated. For simplification of the process, only German sites classified as excellence centers will be included into the analysis, so that consistent national costs (e.g. DRG based, medical supply, labor costs based on tariffs) can be comparable.

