Subgroup analyses are done by sex, tumor stage and (essential) compliance with the protocol (i.e. per protocol analysis). Adverse events are summarized and listed by seriousness, severity and relatedness to treatment. Cumulative survival 30, 36 and 60 months following surgery is estimated by Kaplan-Meier method (with 95% CI according to Greenwood’s formula). Methods for rates and proportions are used to describe hospital mortality and the incidence of post-operative complications. A linear mixed model is fit to health related quality of life data from EORTC questionnaires QLQ-C30, QLQ-STO22, and QLQ-OG25. Cost-effectiveness is determined as the ratio ∆C/∆E where ∆C is the difference in resource use (costs) and ∆E the gain in months of life or in quality of life. The cost-effectiveness (cost per life-month gained or cost per quality-of-life-unit) will be calculated from a societal perspective.

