The systematic review from Haverkamp et al. included 2 retrospective studies on quality of life, these studies suggested a better quality of life after gastrectomy [10]. The Cologne group recently published a retrospective monocentric analysis of own data on long-term quality of life after surgery for adenocarcinoma of the esophagogastric junction type II and detected that health related quality of life after extended gastrectomy with Roux-en-Y reconstruction was indeed superior to that after esophagectomy and gastric tube reconstruction. Patients with cancer-free survival of at least 24 months after esophagectomy or extended gastrectomy for GEJ type II were identified from a prospectively maintained database and EORTC questionnaires were send to these patients. Improved HRQL after gastrectomy was mainly due to less pulmonary symptoms perioperatively and reflux-related symptoms in the long-term follow-up [9].

To date, only retrospective studies are available on surgical therapy of GEJ type II carcinoma, leading to a great controversy about the superior surgical procedure [24]. The CARDIA trial will be the first randomized, clinical trial to determine the surgery of choice for this disease An essential prerequisite for a realistic statement on the therapy of GEJ II tumors is the exact definition of these tumors according to the Siewert classification, which has been described as challenging by other studies [25, 26]. Therefore, all sites will use the endoscopic SOPs in which this is defined in detail. Not only the spread of the main tumor mass but also the tumor extension are considered to ensure resectability of the tumors preoperatively. As perioperative chemotherapy is standard care for all T3–4 or N+ stage patients according to international guidelines [12], chemotherapy is also obligatory for these patients in the current trial. By including patients after chemotherapy, the patient cohort represents the actual group of patients with GEJ II tumors, of which up to 60% are already in an advanced tumor stage at initial diagnosis that requires neoadjuvant therapy [27]. The stratification of randomization is intended to reduce the regional influence of the site or the surgeon on the one hand, and the influence of the tumor stage on the primary outcome on the other.

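### Cost-effectiveness is defined in two incompatible ways: direct cost per QALY in one section, societal cost per life-month or per unit of quality of life in another

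*Protocol article*

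**What the plan says.** Cost-effectiveness is listed among the key secondary endpoints in the Abstract, Objective and Outcome measures of the Protocol article. Two sections then say how it is derived.

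- **Outcome measures:** "a cost effectiveness analysis of both procedures based on direct costs and resulting QALYs will be performed", and "the incremental cost-effectiveness ratio will be calculated". The analysis is limited to German excellence centres so that national costs are comparable.
- **Statistical analysis:** a ratio ∆C/∆E, where ∆C is the cost difference and ∆E is "the gain in months of life or in quality of life". The result is expressed as "cost per life-month gained or cost per quality-of-life-unit" and "will be calculated from a societal perspective". QALYs are not mentioned here.

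Three other places bear on the sign of ∆E. Sample size calculation assumes 45% v 30% survival at 2.5 years in favour of esophagectomy. Background says that some studies found higher quality of life after extended gastrectomy. The Discussion reports a retrospective single-centre analysis in which "health related quality of life after extended gastrectomy with Roux-en-Y reconstruction was indeed superior to that after esophagectomy".

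**The concern.** The two sections differ on both parts of the ratio. The effect is a QALY in one, and life-months or quality of life as alternatives in the other. The costs are direct in one and societal in the other. These choices can give different answers from the same data, and the article does not say which governs.

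The choice of effect matters particularly here because the protocol's own premises point in opposite directions: a survival gain after esophagectomy and a possible loss of quality of life. The wording in Statistical analysis presumes that ∆E is a gain. A life-month ratio ignores any quality loss, and a quality-of-life ratio ignores the survival gain for which the trial is powered. If the definition is settled only after the data are seen, the reported answer to whether esophagectomy is worth its cost could depend on which one is picked.

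**Working it through.** The documents give no cost, effect or cost-effectiveness figure, so none can be reproduced. The check sets the definitions side by side and then works out the sign of each possible ∆E.

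**1. The two definitions**

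| | Outcome measures | Statistical analysis |
|---|---|---|
| Effect | QALYs | life-months, or quality of life |
| Costs | direct | societal |
| Result | one incremental ratio | two alternative ratios |

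**2. Survival input**

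Survival at 30 months is 0.45 v 0.30 (Sample size calculation). The hazard ratio is ln(0.45)/ln(0.30) = 0.663, which matches the stated value.

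Assuming exponential survival, the monthly hazards are -ln(0.45)/30 = 0.0266 for esophagectomy and -ln(0.30)/30 = 0.0401 for gastrectomy. Mean survival restricted to horizon t is (1 - exp(-λt))/λ.

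| Horizon (months) | Esophagectomy | Gastrectomy | Difference | Gastrectomy / esophagectomy |
|---|---|---|---|---|
| 24 | 17.74 | 15.41 | +2.33 | 0.869 |
| 36 | 23.16 | 19.04 | +4.12 | 0.822 |
| 60 | 29.96 | 22.67 | +7.29 | 0.757 |

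On the life-month scale ∆E is therefore positive under the planning assumptions.

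**3. Signs of the two ratios in Statistical analysis**

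The values ∆C = ±5000 and a quality-of-life difference of ±5 points are assumptions chosen only to show signs. The life-month difference is +7.29 (60 months).

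| ∆C | Quality difference | Cost per life-month | Cost per quality point |
|---|---|---|---|
| +5000 | -5 | +686 | -1000 |
| -5000 | -5 | -686 | +1000 |
| +5000 | +5 | +686 | +1000 |
| -5000 | +5 | -686 | -1000 |

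With longer survival and worse quality (first two rows), the two ratios have opposite signs whichever way ∆C goes. Within the last column, -1000 is both costlier-and-worse and cheaper-and-better. Likewise, +1000 is both costlier-and-better and cheaper-and-worse.

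**4. The combined effect**

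Assume a constant mean quality weight in each arm, u_E and u_G. The quality-adjusted difference is u_E × (esophagectomy mean survival) - u_G × (gastrectomy mean survival). It is positive as long as u_E/u_G exceeds the last column of the survival table: about 87% at 24 months, 82% at 36 and 76% at 60.

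For example, take assumed weights of 0.65 v 0.70, a ratio of 0.93. The 24-month difference is (17.74 × 0.65 - 15.41 × 0.70)/12 = +0.062 QALY. The same inputs give -5 points on a 0-100 quality scale. One scale shows a loss where the combined scale shows a gain.

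**The case against.** The strongest counter-argument is that Outcome measures already names a QALY, which combines survival and quality. A reader of Statistical analysis alone might infer that the trial has no combined measure and cannot say whether esophagectomy is worth its cost. The document as a whole does not support that. What stands is that the two sections disagree. The unit of quality of life is also undefined, so it could be meant as a quality-adjusted unit; if so, the text should say so.

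Three further readings go too far:

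- **That the quality-of-life ratio will turn negative.** With a quality loss, this needs ∆C > 0, and the documents give neither a size nor a direction for ∆C. If esophagectomy were cheaper, the ratio would be positive and just as ambiguous.
- **That worse quality of life after esophagectomy is expected.** The cited evidence is retrospective, and the single-centre analysis covered only patients with at least 24 months of cancer-free survival. A negative difference is plausible, no more.
- **That an interval around the ratio would be invalid.** The article plans no interval for cost-effectiveness.

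It is also fair to say that sign ambiguity affects any incremental ratio, and that net benefit and thresholds are detail an article may leave to the full protocol or analysis plan. Their absence is no finding. But the conflicting effect and cost definitions are stated in the article itself.

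**Conclusion.** The point holds as an inconsistency with consequences for what the endpoint can show. The article gives two effect measures and two cost bases for one key secondary endpoint. If survival is longer and quality of life worse after esophagectomy, the two ratios in Statistical analysis have opposite signs for any non-zero ∆C, and neither captures the whole effect. A QALY difference would remain a gain for moderate quality deficits, down to about 87% of the gastrectomy value at 24 months and 76% at 60 months. These limits rest on the planning survival figures, exponential survival and constant quality weights. The questionnaire schedule ends at 24 months, so later horizons also need an assumption about quality.

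The reach is limited. Cost-effectiveness is outside the fixed test sequence of overall survival, R0 resection and quality of life. The primary analysis, type I error and sample size are untouched.

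**What to change.** - In Statistical analysis, define ∆E as the QALY difference, in line with Outcome measures, and drop the stand-alone cost per unit of quality of life as a measure of cost-effectiveness.
- State one cost perspective, and use it in both sections.
- Report ∆C and ∆E separately beside the ratio. Where they have opposite signs, state which procedure dominates instead of interpreting the ratio.
- Optionally, express uncertainty as net benefit (threshold × ∆E - ∆C) over a range of thresholds. This requires the range to be stated.

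The cost is a change of wording and a little more analysis. Outcome measures already commits to QALYs, so redefining ∆E needs no new data.

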### Interim analysis

When half the events (94 deaths) have occurred, an interim analysis will be performed (O’Brien-Fleming type alpha-spending). The outcomes will be evaluated by the DMC. Premature termination of the trial will be considered if the interim analysis or other research show a significant difference in survival between both treatment groups. In addition, the stop-criteria are: < 70% complete resection without tumor residual (R0) in one or both arms as well as > 50% less than 10 lymph nodes harvested in one or both arms. These criteria will be continuously evaluated by the DMC.

## Discussion

In the year 2000, a study on Siewert type I-III GEJ tumors was conducted that compared both surgical approaches. No difference was found between esophagectomy and extended gastrectomy regarding 30-day mortality and 5-year survival [6]. Two years later a retrospective study was conducted in which no statistically significant survival benefit for either one of the surgical approaches was found [11]. Post-operative mortality turned out to be independent of surgical procedure. However, extended gastrectomy was associated with higher microscopic neoplastic invasion of the resection margin than esophagectomy (R0 resection rate: 23.7 and 6.6%, respectively). No differentiation between Type I, II or III was made. Another retrospective research on GEJ type I-III tumors showed that there was no significant difference found in R0 resection, lymph node removal, or post-operative mortality rates with respect to operative approaches. However, gastrectomy was demonstrated to have a significantly worse 5-year survival than esophagectomy, 27 and 37% respectively [24]. In 2014, the Haverkamp et al. systematically reviewed manuscripts published between 1995 and 2013 on surgical strategies of adenocarcinomas of the GEJ and found no clear oncological benefit of either esophagectomy or gastrectomy [10]. More recently, Dutch data suggested that in patients with a type II GEJ adenocarcinoma, a positive circumferential resection margin was more common with gastrectomy. Furthermore, the high prevalence of mediastinal nodal involvement indicates that a full lymphadenectomy of these lymph node positions should be considered. However, no significant difference in 5-year survival was found [10, 20, 25].

The systematic review from Haverkamp et al. included 2 retrospective studies on quality of life, these studies suggested a better quality of life after gastrectomy [10]. The Cologne group recently published a retrospective monocentric analysis of own data on long-term quality of life after surgery for adenocarcinoma of the esophagogastric junction type II and detected that health related quality of life after extended gastrectomy with Roux-en-Y reconstruction was indeed superior to that after esophagectomy and gastric tube reconstruction. Patients with cancer-free survival of at least 24 months after esophagectomy or extended gastrectomy for GEJ type II were identified from a prospectively maintained database and EORTC questionnaires were send to these patients. Improved HRQL after gastrectomy was mainly due to less pulmonary symptoms perioperatively and reflux-related symptoms in the long-term follow-up [9].

To date, only retrospective studies are available on surgical therapy of GEJ type II carcinoma, leading to a great controversy about the superior surgical procedure [24]. The CARDIA trial will be the first randomized, clinical trial to determine the surgery of choice for this disease An essential prerequisite for a realistic statement on the therapy of GEJ II tumors is the exact definition of these tumors according to the Siewert classification, which has been described as challenging by other studies [25, 26]. Therefore, all sites will use the endoscopic SOPs in which this is defined in detail. Not only the spread of the main tumor mass but also the tumor extension are considered to ensure resectability of the tumors preoperatively. As perioperative chemotherapy is standard care for all T3–4 or N+ stage patients according to international guidelines [12], chemotherapy is also obligatory for these patients in the current trial. By including patients after chemotherapy, the patient cohort represents the actual group of patients with GEJ II tumors, of which up to 60% are already in an advanced tumor stage at initial diagnosis that requires neoadjuvant therapy [27]. The stratification of randomization is intended to reduce the regional influence of the site or the surgeon on the one hand, and the influence of the tumor stage on the primary outcome on the other.

Several quality control measures were implemented through every step of the protocol to improve data reliability and therefore the significance of this trial, as the quality of surgery has often been the subject of discussion in clinical gastroesophageal cancer trials. Therefore, only expert high-volume hospitals with a caseload of at least 15 esophagectomies and 10 transhiatal extended gastrectomies per year over the last 3 years are eligible to participate in the trial. Training materials will be provided to all sites before the start of the trial. During the course of the trial, photographs will be taken by the surgeons during each operation, to show the completeness of the lymphadenectomy. They are evaluated by the medical coordinators of the trial and used for continuous feedback to the individual sites. In addition, the DMC can also view the images if there are indications for insufficient surgical quality at an individual site. To ensure not only the surgical but also the pathological quality of the trial, all obligatory lymph node stations are clearly defined and will be sent to the pathology department in separate packages. In addition, a reference pathology was established for the assessment of the resection margins at the UCC and UMCU.

In conclusion, the incidence of GEJ cancer markedly increases. All studies that investigated both surgical procedures only consisted of retrospective series showing ambiguous results on survival and postoperative morbidity.

The CARDIA trial is the first randomized, clinicaltrial that compares transthoracic esophagectomy versus transhiatal extended gastrectomy in patients with GEJ type II tumors. To ensure the data reliability and trial quality, several control measures were implemented in the trial protocol. We hypothesize that transthoracic esophagectomy will allow for a higher rate of radical resections and a more complete mediastinal lymph node dissection, resulting in a longer overall survival, while providing an acceptable quality of life and cost-effectiveness.

### Trial status

Pre-selection visits were conducted at sixteen potential study centers of which twelve were selected for inclusion. The trial centers in Cologne, Leipzig and Munich have been initiated. In addition, the study protocol was approved by two further ethics committees. Recruitment has already started at the University Clinic Cologne, where four patients have been enrolled so far (status May 09th 2020).

## Data Availability

Data sharing is not applicable to this article as no datasets were generated or analysed until this point in the study. The final dataset will be available for the sponsor, the statistiscan, the data management team, and the DMC. The trial interim and final results will be published in a scientific journal. All trial data will be published on behalf of the CARDIA study group, consisting of at least two memebers of every study center. The full protocol and statistical code will not be publicly accessable.

## Abbreviations

AE: Adverse Event
AUC: Area Under the Curve
CT: Computerised Tomography
CRF: Case Report Form
DMC: Data Monitoring Committee
ECCG: Esophageal Complications Consensus Group
ECOG: Eastern Cooperative Oncology Group
EORTC: European Organization for Research and Treatment of Cancer
EOS: End of Study
FEV: Forced Expiratory Volume
GEJ: Gastro-esophageal Junction
HRQL: Health Related Quality of Life
MRI: Magnetic Resonance Imaging
PET: Positron emission tomography
SAE: Serious Adverse Event
ULN: Upper Level of Normal
